### 2.5. Measurements

Demographic, clinical, and lifestyle information collected at the baseline includes age; sex; duration of T2DM; alcohol consumption; smoking history; dietary habits; physical activity; other comorbidities; and medications, including anti-diabetes agents. Physical activities are assessed using the Korean version of the Global Physical Activity Questionnaire (K-GPAQ), a validated tool to assess the effectiveness of interventions promoting physical activity [16,17]. The lifestyle questionnaire administered at the baseline is repeated at week 26 and week 52. Anthropometrics such as height (m), body weight (kg), waist circumference (cm), and blood pressure (mmHg) are measured at every visit. Body composition data are obtained using a bioimpedance analyzer (InBody 720 and 970, InBody Co., Ltd. Seoul, Korea) at the baseline, week 26, and week 52. Laboratory parameters including fasting glucose, HbA1c, and lipid profile are collected at every visit. Serum fasting glucose is analyzed by hexokinase UV. Serum total cholesterol and triglycerides are measured by an enzymatic method, and high-density lipoprotein cholesterol is measured using a selective inhibition method. Low-density lipoprotein (LDL) cholesterol levels are estimated using the Friedewald equation: LDL cholesterol (mg/dL) = total cholesterol (mg/dL) − [triglycerides (mg/dL)/5] − high-density lipoprotein cholesterol (mg/dL) [18]. If the triglyceride level exceeds 400 mg/dL, the LDL cholesterol levels are directly measured using an enzymatic method. All the measurements are performed using a Hitachi 7600 autoanalyzer (Hitachi Instruments Service, Tokyo, Japan). EDTA plasma HbA1c is measured with high-performance liquid chromatography (Tosoh-G8, Tosoh, Tokyo, Japan). C-peptide and urinary albumin-to-creatinine is measured at the baseline and once every 26 weeks. Serum C-peptide is measured using an electrochemiluminescent immunoassay (E170, Roche Diagnostics, Indianapolis, USA). Spot urine albumin and creatinine are measured using a turbidimetric immunoassay and the Jaffe method, respectively. The updated homeostasis model assessment (HOMA2) calculator is used to evaluate HOMA-IR and HOMA-β [19,20]. The HOMA2 model has proven to be more predictive than the original HOMA1 model in Korean patients with T2DM [21].

Hypoglycemic events, including hospitalization or emergency room visits, are evaluated at every visit. Hypoglycemia is defined as blood glucose level < 70 mg/dL or when participants experience symptoms consistent with hypoglycemia, such as sweating, anxiety, or shakiness, and relief of those symptoms occurs following ingestion of glucose [22,23]. Diabetes management strategies, such as SMBG frequency, physical activity, and diet, are obtained at every visit. Quality of life is assessed using the Korean version of the Euro-QOL (EQ-5D-5L) instrument at the baseline and once every 26 weeks [24,25]. The EQ-5D-5L comprises five dimensions (mobility, self-care, usual activities, pain/discomfort, and anxiety/depression) rated on a scale of five (none, slight, moderate, severe, and extreme). User satisfaction with the mobile application will be surveyed in Groups 2 and 3 at the end of the study. Adherence will be assessed by evaluating the scheduled visits, SMBG frequency, maintenance of physical activity and diet record, and achievement of the HbA1c goal. Any adverse events occurring during the trial will be monitored until resolution and reported as required.

### 2.6. Sample Size Calculations

Based on the previous studies [7,8,26], we assumed a mean difference in the HbA1c level of at least 0.60 between the control and intervention groups and a standard deviation within a group of 0.75 after six months. In a single-factor analysis of variance (ANOVA), it was determined that a sample size of 219 (73 per group) would yield 90% power and a 0.05 significance level. We planned both an interim and a final analysis. Therefore, RB = (2, 0.05, 0.1) = 1.007 was applied as the O’Brien–Fleming test. Finally, a total of 282 subjects (94 per group) are required with a predictive dropout rate of up to 20% to achieve 73 subjects per group. This is an ongoing trial in which 181 participants have been enrolled to date.

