## 1. Introduction

Diabetes mellitus is a major health concern affecting 463 million people worldwide [1]. Due to related complications and comorbidities, an estimated 4.2 million deaths were attributed to diabetes in 2019 [1,2]. Intensive glycemic control can reduce morbidity and mortality by decreasing micro- and macrovascular complications [3]. However, to achieve glycemic goals, in addition to medical treatment, self-management strategies, including diet, exercise, and self-monitoring of blood glucose (SMBG), are essential. Its complex nature challenges patients and providers to properly manage diabetes, with only 25.1% of patients meeting the glycated hemoglobin (HbA1c) target of <6.5% and 52.6% meeting the HbA1c target of <7.0% in Korea [4]. Furthermore, only 8.4% of patients with diabetes met combined glycemic, lipid, and blood pressure goals [4]. In the United States, 37.0% and 7.3% of patients, respectively, met the HbA1c target of <7.0% and combined glycemic, lipid, and blood pressure goals [5]. Taken together, these data indicate how difficult it is to achieve target glycemic goals despite remarkable advances in anti-diabetes medications.

In response to this concern, mobile applications have recently emerged as a promising technology to enable effective self-management of diabetes. These tools can aid patients with diabetes by increasing awareness of and modifying behavior through reminder and/or feedback [6]. Such applications allow remote assessment and prompt intervention by healthcare professionals (HCPs) between visits, especially in urgent situations, such as hypoglycemia or severe hyperglycemia [7]. Mobile applications have been reported as superior to interventions such as text messaging, mobile device use, or conventional self-management. Several meta-analyses have shown that use of mobile applications can reduce HbA1c levels by 0.5%, with an even greater reduction when combined with HCP feedback [7,8,9].

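### The inputs printed in section 2.6 need 31 to 41 patients per group, not 73, and 73 per group gives over 99% power at the 0.05 level, not 90%

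*Protocol article*

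**What the plan says.** Section 2.6 of the protocol article gives nearly everything needed to check its sample size.

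- Effect: "we assumed a mean difference in the HbA1c level of at least 0.60 between the control and intervention groups".
- Variability: "a standard deviation within a group of 0.75 after six months".
- Method: "In a single-factor analysis of variance (ANOVA"), with three groups. Section 2.7 gives 1:1:1 allocation.
- Result: "it was determined that a sample size of 219 (73 per group) would yield 90% power and a 0.05 significance level".
- Group-sequential factor for one interim and one final analysis: "RB = (2, 0.05, 0.1) = 1.007 was applied".
- Final size: "a total of 282 subjects (94 per group) are required with a predictive dropout rate of up to 20% to achieve 73 subjects per group".

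The only element left open is how the two app arms are placed relative to each other and to control. Section 2.8 separately prints significance levels of 0.005 (interim) and 0.0048 (final), and Bonferroni post-hoc comparisons.

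**The concern.** A difference of 0.60 with an SD of 0.75 is a standardised difference of 0.60/0.75 = 0.8. That is a large effect, and 73 per group is far more than 90% power at 0.05 should require. The figure of 73 is stated before the dropout allowance, so dropout cannot explain the excess.

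The mismatch affects how the trial is read. If 0.60 and 0.75 were the working inputs, the trial can detect differences well below 0.60, and a null result would be informative there. If the working SD was larger, or the working difference smaller, 90% may be correct, but then a null result says less than the printed inputs imply and there is little room for lost patients. The text does not let a reader tell which case applies.

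**Working it through.** **Inputs.** Difference 0.60, SD 0.75, three equal groups, alpha 0.05, power 90% (sections 2.6 and 2.7). The mean pattern is not stated, so two are used:

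- A: 0, 0.6, 0.6. Both app arms differ from control by 0.60, the natural reading of the text.
- B: 0, 0.3, 0.6. Equal spacing, which gives the lowest F-test power for a maximum difference of 0.60.

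**Formula.** Power = P(F′ > F crit), where F′ is noncentral F with 2 and 3(n − 1) degrees of freedom and noncentrality λ = n × Σ(μᵢ − μ̄)² / SD². SD² = 0.5625.

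- A: mean 0.4, Σ = 0.16 + 0.04 + 0.04 = 0.24, so λ = n × 0.24/0.5625 = 0.4267n.
- B: mean 0.3, Σ = 0.09 + 0 + 0.09 = 0.18, so λ = n × 0.18/0.5625 = 0.32n.

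**Attempt to reproduce 73 per group (alpha 0.05, 90% power).**

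| Pattern | Smallest n per group | λ at that n | Power | Total |
|---|---|---|---|---|
| A | 31 | 13.23 | 90.3% | 93 |
| B | 41 | 13.12 | 90.3% | 123 |

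The figure is not reproduced: 73 is 73/41 = 1.8 to 73/31 = 2.4 times the requirement. The 1.007 factor, rounded up, moves 31 and 41 only to 32 and 42.

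**Power at 73 per group (alpha 0.05).** A: λ = 31.15, power 99.9%. B: λ = 23.36, power 99.4%.

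**Difference detectable with 90% power at 73 per group (SD 0.75, alpha 0.05).** About 0.39 if both app arms differ from control equally, and about 0.44 if the means are equally spaced.

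**Other ways of sizing with 0.60, SD 0.75 and 90% power.**

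| Method | n per group |
|---|---|
| Two-sample t-test, two-sided 0.05 | 34 |
| Two-sample t-test, 0.05/3 | 44 |
| ANOVA at 0.05/3 | 39 (A), 52 (B) |
| ANOVA at 0.0048 | 48 (A), 63 (B) |
| ANOVA at 0.0048/3 = 0.0016 | 55 (A), 73 (B) |

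Only the last row reaches 73, and only for pattern B. It contradicts the 0.05 given in the same sentence as the 73.

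**Inputs that would give 73 at alpha 0.05.** For equally spaced means, a difference of 0.60 with SD 1.0 and a difference of 0.45 with SD 0.75 have the same standardised difference (0.6). Each needs 72 per group (λ = 72 × 0.18 = 12.96, power 90.3%), and 72 × 1.007 = 72.5, rounded up to 73. Neither set is documented.

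**Power at 73 per group at the level of 0.0048 printed in section 2.8.** A: 99.1%. B: 94.9%.

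**The case against.** The strongest objection is that the printed inputs make the trial larger than necessary, so nothing is at risk and this is only a reporting slip. The direction is right: the discrepancy does not show an underpowered trial, and enrolment need not change. It does not follow that the text can stand. The printed inputs, sample size and power cannot all be true, and the comfortable margin exists only if 0.60 and 0.75 are the real inputs. The 181 enrolled out of 282 is progress in an ongoing trial, not a shortfall.

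A second objection is that a stricter alpha could explain 73. The 0.0016 route does reach it, so a misprinted SD or difference is not the only possible source. But that route departs from section 2.6's own alpha, so it does not rescue the statement. It does show that over 99% holds only at 0.05 and should not be adopted as the new power figure before the final level is settled.

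Two further criticisms may tempt a reader, and the article supports neither.

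- **That 282 does not follow from 73 with 20% dropout.** Exact inflation gives 73/0.8 = 91.25, so 92 per group (276). With the 1.007 factor first, 73.5 rounds up to 74, and 74/0.8 = 92.5, so 93 per group (279). The stated 94 is one or two per group higher. It leaves 94 × 0.8 = 75.2 completers, which meets the aim of 73. That 94 would tolerate 1 − 73/94 = 22% dropout is consistent with planning for up to 20%.
- **That 0.60 conflicts with the Introduction.** The Introduction says "Several meta-analyses have shown that use of mobile applications can reduce HbA1c levels by 0.5"%, but the same sentence reports a larger reduction when feedback from healthcare professionals is added, and one arm of this trial has that feedback.

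**Conclusion.** The point holds for the base calculation. With a difference of 0.60, SD 0.75, three-group ANOVA, alpha 0.05 and 90% power, the requirement is 31 to 41 per group (93 to 123 in total), against the 73 (219) stated. At 73 per group the power at 0.05 is 99.4% to 99.9%. The range comes only from the unstated mean pattern. If the differences exceed 0.60, as the words at least allow, the requirement falls further.

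A reader might infer that the SD was really 1.0, or the difference really 0.45. Both fit the arithmetic, but neither appears in the article and another route also reaches 73, so the source of the error remains open. The step from 73 to 94 per group is slightly conservative and is not part of the finding.

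**What to change.** Re-run the calculation and correct section 2.6 so that inputs, sample size and power agree, in one of two ways:

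1. If other inputs produced 73, print them: SD, difference, the assumed pattern of the three means, and alpha.
2. If 0.60 and 0.75 are correct, keep them and replace the 90% with the power that 73 per group provides, together with the detectable difference. At alpha 0.05 these are over 99% and about 0.39 to 0.44, depending on the mean pattern.

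In either case, first reconcile the 0.05 in section 2.6 with the final level of 0.0048 in section 2.8, and compute any restated power at the reconciled level.

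The cost is one recalculation and a rewording of section 2.6. Enrolment does not change.

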### 2.7. Randomization

Randomization is performed to ensure scientific validity of the clinical trial by maximizing comparability between the groups and to prevent subjective involvement by investigators. An independent statistician having no contact with participants performs the randomization process. Eligible participants who provide written informed consent are randomly assigned to one of the three groups in a 1:1:1 ratio. Random numbers are generated using SAS version 9.3 (SAS Institute Inc., Cary, NC, USA) and sequentially numbered, opaque, sealed envelopes are used for allocation. Stratification is by study site and baseline HbA1c of 8.5% using the stratified permutated block randomization method. As this study is an open-label design, group assignment is known to the participants and HCPs after randomization.

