### 2.3. Eligibility

Eligible participants must meet all the inclusion criteria: (1) patients with T2DM who need SBMG and who underwent self-management training; (2) age of 19–74 years; (3) HbA1c ≥ 7.5%; (4) body mass index (BMI, calculated as kg/m^2^) ≥ 18.5 kg/m^2^; (5) ability to use a smartphone; and (6) written informed consent.

Exclusion criteria are: (1) insulin pump use; (2) estimated glomerular filtration rate < 30 mL/min/1.73 m^2^; (3) heart failure (New York Heart Association class III–IV); (4) diagnosis of cancer within five years; (5) recipient of an organ transplant or need in long-term immunosuppressant therapy; (6) difficulty in exercise and physical activity due to spinal disease (intervertebral disc prolapse, spinal stenosis, etc.), joint disease, or major surgery at the time of screening; (7) plan to receive surgery that could limit physical activity during the study period; (8) pregnant or breastfeeding; (9) plan to become pregnant or disagreement with using adequate contraception during the study period; (10) participation in another clinical trial (other than an observational one) within 90 days; and (11) inappropriate candidate as judged by an investigator.

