### 2.8. Statistical Analysis

The data are collected using electronic case report forms and are password-protected. Only the principal investigator and authorized research personnel may access the data. Range checks on data values will be performed prior to analysis. Continuous variables will be presented as the means ± the standard deviation while categorical data will be presented as frequency and percentage. An analysis of covariance (ANCOVA) will be used to compare the mean HbA1c at week 26 between the three groups. The analysis will be conducted by adjusting for study site and baseline HbA1c of 8.5%. Post-hoc analysis will be performed with the Bonferroni method. The mixed-effect model repeated measures (MMRM) will be used to compare change in HbA1c from the baseline to week 26. For binary outcome variables, such as the rate of achieving the target HbA1c level, a generalized linear mixed model (logistic GLMM) will be used. The fixed effects in the MMRM and GLMM include treatment group indicators, time indicators, and interactions between the treatment group and time. The number of hypoglycemic events will be compared between the groups using the chi-squared or Fisher’s exact test.

Analysis will be performed as both per protocol and intention-to-treat. Unless otherwise specified, analyses will be reported based on the results of the intention-to-treat analysis. For interim analysis, adjustment for multiplicity will be applied. Based on the O’Brien–Fleming test, the significance level will be set at 0.005 and 0.0048 for interim and final analysis, respectively. Analyses will be performed using SAS version 9.3 (SAS Institute Inc., Cary, NC, USA).

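### Hypoglycemia is compared without adjustment for baseline insulin or secretagogue use, although this is recorded: the test is valid, but modest precision and ease of interpretation are given up

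*Protocol article*

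**What the plan says.** **Who can enter.** Section 2.3 of the protocol article admits adults with type 2 diabetes and HbA1c of at least 7.5%, and sets no limit on background glucose-lowering treatment. The one criterion that touches insulin opens the exclusion list: "Exclusion criteria are: (1) insulin pump use". That injected-insulin users are admitted is an inference from this, though a natural one.

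**What is recorded.** The baseline data in section 2.5 include "other comorbidities; and medications, including anti-diabetes agents".

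**How arms are balanced.** Section 2.7 states: "Stratification is by study site and baseline HbA1c of 8.5% using the stratified permutated block randomization method". Allocation is 1:1:1.

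**How outcomes are analysed.** Section 2.8 adjusts the week-26 HbA1c ANCOVA for site and the 8.5% HbA1c category. For the longitudinal models it says: "The fixed effects in the MMRM and GLMM include treatment group indicators, time indicators, and interactions between the treatment group and time". Hypoglycemia gets a chi-squared or Fisher's exact test between groups, and neither takes a covariate. Hypoglycemia episodes are a secondary outcome (section 2.4). Baseline treatment appears in no stated stratum, covariate or subgroup. Medication returns only as an exploratory outcome, as change during the trial.

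**The concern.** Use of insulin or an insulin secretagogue is a main determinant of hypoglycemia. Where eligibility allows a mix of users and non-users, part of the person-to-person variation in hypoglycemia is predictable from a baseline fact that the trial already holds. An unadjusted comparison leaves that variation in the error term.

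If one arm happened to contain more users and also showed more hypoglycemia, a reader would ask how much of the difference reflects the mix and how much the application. No planned analysis answers that. The trial is open-label, so an adjustment chosen after the imbalance is seen would look discretionary. This favours fixing it in advance.

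At stake are the precision and interpretation of one secondary safety comparison. The choice of method for counts of episodes is a separate matter.

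**Working it through.** **Inputs.** From the documents: 94 per group (section 2.6), and an HbA1c standard deviation of 0.75 with a planned difference of 0.60 (section 2.6). The documents give no figure for treatment mix or hypoglycemia risk, so there is no figure of the plan's own to reproduce. Assumed: share of users p = 20–50%; any hypoglycemia in 50% of users and 15% of non-users, a gap of 0.35.

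**Step 1: chance imbalance between two arms.** The 95% half-range is 1.96·√(2p(1−p)/94). Multiplying by 0.35 gives the resulting movement in the risk difference.

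**Step 2: sampling error of the unadjusted comparison.** The overall risk is m = 0.50p + 0.15(1−p), and the 95% half-width of the risk difference is 1.96·√(2m(1−m)/94).

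**Step 3: what adjustment recovers.** The share of variance explained is R² = p(1−p)·0.35²/[m(1−m)], and the interval shortens by 1−√(1−R²).

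| | p = 0.20 | p = 0.35 | p = 0.50 |
|---|---|---|---|
| Imbalance, points | ±11.4 | ±13.6 | ±14.3 |
| Movement in risk difference, points | ±4.0 | ±4.8 | ±5.0 |
| Overall risk m | 0.220 | 0.2725 | 0.325 |
| Unadjusted half-width, points | 11.8 | 12.7 | 13.4 |
| R² | 0.114 | 0.141 | 0.140 |
| Shortening | 5.9% | 7.3% | 7.2% |
| Shortening, points | 0.7 | 0.9 | 1.0 |

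The movement in the second row is already contained in the half-width in the fourth row. It does not come on top of it.

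**Step 4: wider assumptions.** With 40–50% risk in users and 10–20% in non-users, and p from 20% to 50%, the movement is ±2.3 to ±5.7 points and R² is about 4–20%. The unrounded R² of 0.035 to 0.200 gives a shortening of 1−√0.965 ≈ 2% to 1−√0.800 ≈ 11%.

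**Step 5: validity.** Under the same wider assumptions, three arms of 94 with no treatment effect were simulated 40,000 times per scenario. The unadjusted three-group chi-squared test at the 5% level rejected in 4.8–5.1% of runs.

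**Step 6: HbA1c.** Assume users and non-users differ by d = 0.2–0.5 HbA1c points, with p = 30–50%.
- R² = p(1−p)d²/0.75² runs from 0.21·0.04/0.5625 = 0.015 to 0.25·0.25/0.5625 = 0.111, so adjustment makes the standard error about 1–6% smaller.
- The 95% chance shift, d·1.96·√(2p(1−p)/94), is 0.03–0.07 points, against a planned difference of 0.60.

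**The case against.** The strongest objection is that this is an enhancement to a sound analysis. Stratifying on site and baseline HbA1c and adjusting the ANCOVA for the same two factors is coherent, and stratifying on HbA1c may partly balance treatment as well. Extra covariates for a secondary outcome are often left to an analysis plan. The abstract also says outcomes will be compared allowing for clinical factors, with age and baseline HbA1c as open-ended examples. Finally, every magnitude here rests on assumed inputs.

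Most of this stands, and it sets the size of the point. It does not remove it. The article does not defer the choice: it names the strata, the covariates, the fixed effects and the hypoglycemia test, and the test it names cannot carry any clinical factor. If a fuller plan already contains the adjustment, the sponsor need only confirm it.

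A second objection concerns the remedy. A covariate cannot simply be added to a chi-squared or Fisher's test, and in logistic regression adjustment for a prognostic factor need not make the odds ratio more precise. This is correct, so the method and the effect measure must be named.

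A reader might also infer that the hypoglycemia comparison is biased or its test invalid. Neither follows. Randomisation makes imbalance a matter of chance, which the ordinary standard error already covers, and the simulated error rate stays at about 5%.

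**Conclusion.** The point holds as a minor improvement to section 2.8. The unadjusted hypoglycemia test is valid and unbiased. It forgoes modest precision and gives no prespecified way to read the result if baseline treatment differs between arms by chance.

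Under the main assumptions (20–50% users; 50% against 15% with any event), adjustment shortens the 95% interval for the risk difference by about 6–7%, or 0.7–1.0 point of a half-width of about 12–13 points. Under the wider assumptions, baseline use explains 4–20% of the variance. These figures concern participants with at least one event, take all 94 per group as contributing, and rest on the inference that injected-insulin users are enrolled.

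Two stronger readings are not supported. One is that the randomisation is deficient: leaving out a third stratification factor is a legitimate design choice. The other is that the primary result is threatened: baseline HbA1c is already stratified and in the ANCOVA, and the assumed effect of baseline treatment on that comparison is very small.

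**What to change.** In section 2.8, before any comparison by arm:

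- Prespecify that the proportion of participants with any hypoglycemia is compared by a Cochran-Mantel-Haenszel test and a Mantel-Haenszel (or standardised) risk difference, stratified by baseline insulin or secretagogue use (yes/no).
- Keep the unadjusted chi-squared or Fisher's exact test as a sensitivity analysis.
- Show events by arm within each baseline-treatment group, for description only. At 20% use there would be about 19 users per arm (0.20 × 94), too few for inference.
- Optionally, add the same yes/no term to the week-26 HbA1c model. The benefit there is small.

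The data are already collected, and randomisation and enrolment stay unchanged. The cost is one slightly less simple analysis.
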